## Abstract

**Background:**

Soft tissue sarcomas (STS), have significant inter- and intra-tumoral heterogeneity, with poor response to standard neoadjuvant radiotherapy (RT). Achieving a favorable pathologic response (FPR ≥ 95%) from RT is associated with improved patient outcome. Genomic adjusted radiation dose (GARD), a radiation-specific metric that quantifies the expected RT treatment effect as a function of tumor dose and genomics, proposed that STS is significantly underdosed. STS have significant radiomic heterogeneity, where radiomic habitats can delineate regions of intra-tumoral hypoxia and radioresistance. We designed a novel clinical trial, Habitat Escalated Adaptive Therapy (HEAT), utilizing radiomic habitats to identify areas of radioresistance within the tumor and targeting them with GARD-optimized doses, to improve FPR in high-grade STS.

**Methods:**

Phase 2 non-randomized single-arm clinical trial includes non-metastatic, resectable high-grade STS patients. Pre-treatment multiparametric MRIs (mpMRI) delineate three distinct intra-tumoral habitats based on apparent diffusion coefficient (ADC) and dynamic contrast enhanced (DCE) sequences. GARD estimates that simultaneous integrated boost (SIB) doses of 70 and 60 Gy in 25 fractions to the highest and intermediate radioresistant habitats, while the remaining volume receives standard 50 Gy, would lead to a > 3 fold FPR increase to 24%. Pre-treatment CT guided biopsies of each habitat along with clip placement will be performed for pathologic evaluation, future genomic studies, and response assessment. An mpMRI taken between weeks two and three of treatment will be used for biological plan adaptation to account for tumor response, in addition to an mpMRI after the completion of radiotherapy in addition to pathologic response, toxicity, radiomic response, disease control, and survival will be evaluated as secondary endpoints. Furthermore, liquid biopsy will be performed with mpMRI for future ancillary studies.

**Discussion:**

This is the first clinical trial to test a novel genomic-based RT dose optimization (GARD) and to utilize radiomic habitats to identify and target radioresistance regions, as a strategy to improve the outcome of RT-treated STS patients. Its success could usher in a new phase in radiation oncology, integrating genomic and radiomic insights into clinical practice and trial designs, and may reveal new radiomic and genomic biomarkers, refining personalized treatment strategies for STS.

**Trial registration:**

NCT05301283.

**Trial status:**

The trial started recruitment on March 17, 2022.

## Background

Minimal progress has been made in the management of soft tissue sarcoma (STS) over the past several years [1]. The underlying difficulty behind this effort is multifactorial, as sarcoma is a rare disease entity representing approximately 1% of cancer incidence in the United States and possesses significant intra- and inter-tumoral heterogeneity, consisting of dozens of histologies with varying clinical behaviors [2]. Despite this known diversity, the current standard of care is a uniform, conventionally fractionated radiation dose delivered homogenously, followed by a planned operation, regardless of histology, grade, or obvious radiographic intratumoral heterogeneity [3–5]. This treatment algorithm results in local recurrence rates ranging from 10 to 20%, the majority of which occur within the radiotherapy treatment field. In addition, standard neoadjuvant radiation treatment achieves a favorable pathological response (FPR ≥ 95% cellular response) in only 8% of cases [6]. These findings clinically support the claim that STS may be inherently radioresistant [1, 7–9], which has also been described radio-biologically, with an alpha/beta ratio ranging from 2 to 6 [10, 11].

In recent studies, we have developed the genomic adjusted radiation dose (GARD), an RT-specific metric that estimates the clinical effect of a given RT dose for an individual tumor. GARD is based on the gene expression-based radiosensitivity index (RSI), a clinically validated genomic signature of cellular radiosensitivity and the linear quadratic model [12, 13]. In a pan-cancer analysis including 1615 patients in seven different disease sites, GARD outperformed RT dose (EQD2) by its association with clinical outcome (overall survival and recurrence risk), and its prediction and quantification of RT benefit for each individual patient [12]. STS was found to have a broad range of radiosensitivity across various histologies, where the ideal neoadjuvant dose for highly radioresistant STS histologies is a BED_3.29_ ≥97 Gy, which translates to 57.5 Gy in 25 fractions [11]. This is consistent with the improved local control seen with neoadjuvant simultaneous integrated boost in retroperitoneal sarcoma, where 57.5 Gy in 25 fractions had a higher 5-year abdominopelvic control (96% vs. 70%, *p* = 0.046), when compared to standard fractionation RT [14].

Given its ability to quantify RT benefit, we have proposed that GARD could be utilized to design clinical trials. To support this, we have demonstrated that GARD-based model predictions for uniform dose escalation (as in RTOG 0617 for NSCLC) or uniform de-escalation in HPV + oropharynx cancer (as in HN005) align with the clinical results reported for the actual trial. There are two approaches to GARD-based clinical design: (1) Uniform GARD-optimized dose and (2) Personalized GARD-optimized dose. The first approach is focused on diseases where GARD estimates patients are either primarily under/over-dosed with RT and thus a single escalated/de-escalated RT dose is predicted to impact the overall treatment benefit for the population. In the second approach, no single RT dose is identified that can improve the overall outcome of the population and only a patient-specific personalized approach is predicted to work. GARD-optimization models propose that in STS a uniform approach would be successful.

Although, STSs are primarily considered radioresistant, gene expression and RSI variability exists both between tumors and within each tumor [15], which may account for the differences in radiation responses to subpopulations within the tumor [16]. In addition, tumor hypoxia [17] might be a contributor factor to this phenotype, with radiographically identifiable regions within STS exhibiting poor perfusion and dense cellularity [18–20]. From a prognostic standpoint, tumor hypoxia has been associated with a more aggressive phenotype [21] and a higher risk of metastatic disease [22, 23]. This association may explain the distant control and overall survival benefit observed when FPR is achieved, in addition to the expected locoregional control benefit [24, 25], which may be in part due to the improved R0 (i.e., negative tumor at ink) resection rates in patient that achieve FPR^6 26^. Therefore, efforts to personalize treatment both inter- and intratumorally are required to optimize FPR rates and, in turn, patient outcomes.

Advances in our understanding of tumor heterogeneity, radiosensitivity, and radiomics have provided the opportunity to personalize our radiation treatment planning and provide directed treatment escalation of STS, thereby improving clinical responses and outcomes. These improvements have been facilitated by advances in tumor imaging, much of which is part of the standard workup for STS, including computed tomography (CT) and magnetic resonance imaging (MRI). Less commonly used MRI sequences, such as apparent diffusion coefficient (ADC) and dynamic contrast enhanced (DCE) images, demonstrate cellularity and hypoxia within STS [18–20] and are prognostic for tumor response to radiotherapy [27–32] as early as week two of treatment [28]. By using these sequences, MRI habitat analyses identify cellular subpopulations that may represent a distinct tumor biology [3, 4, 33]. Overlaying of these sequences, which identify cellular density, hypoxia, and perfusion, has allowed for distinction between regions of viable oxygenated, viable hypoxic, and necrotic cells [16, 29, 34, 35]. The focal dose escalations would be limited to regions within the gross tumor volume (GTV), while maintaining the same microscopic dose for the broader clinical target volume (CTV) coverage, without a significant change in dose to the surrounding normal tissue [36]. Therefore, STS is the ideal disease to utilize genomics and radiomics to effectively personalize radiation treatment, optimizing pathologic response, R0 resection, and outcome.

In this study, we describe a prospective clinical trial to test a novel genomic-based RT dose optimization algorithm (GARD), utilizing radiomics-habitat directed targeting, to improve the clinical outcomes for soft tissue sarcoma. GARD-based clinical trial modeling proposes that selectively increasing dose (60 and 70 Gy in 25 fractions) to the radioresistant half of the tumor will triple the number of patients that experience a favorable pathological response, compared to standard of care dose (50 Gy in 25 fractions). To identify which intratumoral regions would benefit from the higher optimized doses, we integrate a radiomic habitat-based approach, directing the GARD-optimized RT dose to the cell dense and hypoxic MRI based subpopulations. This isotoxic approach is hypothesized to result in acceptable normal tissue dosing for the GARD-optimized RT dose, focally escalating radiation dose levels with the use of modern radiation techniques (e.g., simultaneous integrated boost [SIB]). The hypofractionation offers a higher biological effect on these low α/β regions, providing an avenue for safely improving FPR rates without significantly increasing toxicity, which is associated with improved local control, distant control, and overall survival [24–26, 37]. With improved understandings of tumor heterogeneity, radiosensitivity, and radiomics, our goal is to personalize radiation treatment for each patient.

### Aims

The primary aim of the study is to determine whether radiomic habitat directed GARD-optimized RT dose escalation can significantly increase the favorable pathologic response rate by > 3 fold over historic standard neoadjuvant radiotherapy (7.9%) to 24%. In addition to safety and feasibility of this approach, we will investigate predictors of response, radiomics-genomic correlation, circulating biomarkers of response, and the genomic heterogeneity within these habitats to create non-invasive radiomic biomarkers for further prospective validation.

## Methods/design

### Ethics approval

The study is approved by the Institutional Review Board (IRB) of the H. Lee Moffitt Cancer Center and Research Institute (MCC IRB #21,136). The HEAT trial is registered at the US National Institutes of Health (ClinicalTrials.gov) #NCT05301283. The current protocol is version 1.4 dated May 5, 2023.

### Study design

This is a non-randomized, single arm, single institution, Phase 2 study of adult patients with non-metastatic high-grade deep STS (grade ≥ 2). The H. Lee Moffitt Cancer Center and Research Institute is responsible for the coordination and trial management, as well as quality assurance including reporting, monitoring, and database management. The study schema is depicted in Fig. 1.

**Fig. 1 Fig1:**
[figure not shown]
Trial schema. Radiation therapy begins between visit 1 and visit 2. All patients will be seen during weekly treatment visits throughout radiation therapy. Radiation therapy ends between visit 2 and visit 3. Surgical resection occurs between visit 3 and visit 4

We hypothesize that GARD-optimized RT dose for STS (60 to 70 Gy in 25 fractions), delivered to MRI defined radiomic habitats will triple the FPR rate as defined by response in the surgical specimen of ≥ 95% cellular response. With 36 evaluable patients, this study has 81.8% power to detect an increase in the FPR rate from 7.9% (benchmark selected based on historical data) to 24%, with a one-sided alpha = 0.05. A Z-test with continuity correction will be used to determine changes in the FPR. Assuming 15% of patients will be unevaluable, up to 43 patients will be enrolled within 24 months. This trial uses Fleming’s 3-stage design, in which stage 1 accrual is 13 evaluable patients over 6 months, with a projected accrual rate of 2 patients per month. Stage 2 accrual is 10 and the final stage accrual is 13. Assuming 50% of the eligible patients over a 12-month period enroll in this trial, 3 patients per month will enroll.

### Inclusion and exclusion criteria

Patients with a histologically or cytologically confirmed diagnosis of high-grade (grade ≥ 2) STS of the deep trunk and/or extremity that has been deemed resectable prior to the start of the trial can be included in this study. The main exclusion criteria are metastatic disease, contraindications to MRI, or prior overlapping radiation therapy fields. All inclusion and exclusion criteria are shown in Table 1.

**Table 1 Tab1:** Inclusion and exclusion criteria

Criteria	Details
Inclusion	1. Provision of signed and dated informed consent form 2. Stated willingness to comply with all study procedures and availability for the duration of the study 3. Age ≥ 18 years 4. For women of childbearing potential: use of highly effective contraception for at least 1 month prior to screening and agreement to use such a method during study participation and for an additional 52 weeks after the end of RT 5. For males of reproductive potential: use of condoms or other methods to ensure effective contraception with partner 52 weeks after RT 6. Agreement to adhere to Lifestyle Considerations (see section 5.3) throughout study duration 7. Pathologically (histologically or cytologically) proven diagnosis of high-grade (grade 2 or 3) STS of the deep trunk and/or extremity. Clinical evidence should be documented, and may consist of pathology or imaging, and should be sufficient to estimate the size of the primary (for T stage) 8. Primary site deemed resectable prior to the start of trial 9. AJCC 8th edition staging T1-4 N0 M0 10. Patients must have clinically or radiographically evident measurable disease at the primary site 11. Pre-RT MRI within 4 weeks of the start of RT 12. ECOG Performance Status 0 to 3 13. Deemed a surgical candidate 14. Patient agrees to blood and plasma preservation for future analysis.
Exclusion	1. Contraindications to an MRI 2. Positive urine pregnancy test 3. Gross total excision of primary STS, including an unplanned excision 4. Superficial sarcoma located primarily in the subcutaneous or cutaneous tissue 5. Evidence of metastatic disease 6. Prior RT to the region of the study cancer that would result in overlap of RT fields 7. Patients with a medical condition or social situation that, at the discretion of the principal investigator, would preclude them from completion of the trial

Abbreviations. AJCC: American Joint Committee on Cancer; ECOG: Eastern Cooperative Oncology Group; MRI: magnetic resonance image; RT: radiation therapy; STS: soft tissue sarcoma

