#### GARD modeling of STS

In previous studies we generated the distribution of GARD for 231 STS patients, assuming standard of care neoadjuvant RT dose (50 Gy in 25 fractions), and an average beta of 0.045 [11, 38, 39]. As shown in Fig. 2, GARD ranged from 22.96 to 31.37, with a higher GARD predicting a higher probability of tumor response. In addition, since the GARD calculation is based on the linear-quadratic model, the distribution curve (Fig. 2) has a linear region where there is a rapid increase in GARD. We modeled two possible scenarios. In the first scenario, we assumed that the baseline response to neoadjuvant RT (based on SOC dose) is ∼ 8% (7.9%), as demonstrated in the recent phase 2/3 clinical trial [6]. In a second scenario, a review of our center’s experience revealed that 37 of 202 (18.3%) STS patients treated with standard neoadjuvant RT alone experienced an FPR. Next, we identified approximately the top 8th and 18th percentile values in the GARD distribution (31.37 and 22.96), the highest 8% and 18% radiosensitive sarcomas are most likely to achieve a FPR, which we hypothesize are the GARD target values that optimize clinical outcome. It should be noted that the hypothesized GARD targets are both located after the linear region of GARD suggesting that uniform increase in dose are likely to impact the outcome of these patients. We next modeled the impact on GARD distribution if the dose was 60 and 70 Gy. As shown in Fig. 2, the number of patients that are predicted to achieve each GARD target (31.37 and 22.96) would increase with homogenous dose to 60 Gy (15.2–26.8%) and 70 Gy (26.8–60.2%), depending on true baseline response rate.

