### Statistical considerations

#### Sample size and interim analyses

The primary endpoint is evaluating the FPR rate of patients with resectable non-metastatic high-grade STS treated to GARD-optimized RT dose utilizing MRI habitat–directed neoadjuvant radiation therapy. GARD-based modeling predicted that increasing the dose (60 to 70 Gy) would triple the FPR to an average of > 24.3%. The null hypothesis that the true FPR is 7.9%, which will be tested against a 1-sided alternative hypothesis that the FPR is 24%. We determined the sample size of a maximum of 43 patients using Fleming’s three-stage optimal design, which has a one-sided significance level of 5% and a power of 81.8% if the true FPR is 24% under the alternative hypothesis. The trial is carried out in 3 stages. In the first stage, a total of 13 evaluable patients will be accrued. If there are at least five FPRs among these 13 patients, the study will be considered a success, but will continue to accrue to 23 total patients to obtain further sufficient information about primary and secondary endpoints. Otherwise, it will move onto the second stage that will accrue an additional 10 evaluable patients. If there are two or fewer FPRs in the total of 23 subjects in the second stage, the trial will be stopped for futility. If there are ≥ 5 FPRs among these 23 patients, the study will be considered a success and accrual would end after the 23 total patients. Otherwise, ten additional evaluable patients will be accrued in the final third stage, resulting in a total sample size of 36. The null hypothesis will be rejected if there are ≥ 7 FPRs among these 36 subjects. Considering a dropout rate of 15%, approximately 43 subjects will be enrolled. If the true response rate is 7.9%, then the probability of stopping early for futility is 71.4%, the probability of stopping early for success is 4.4%, and the expected sample size is 26.2. When the trial is considered successful at the first or second interim analysis, a total of 23 evaluable patients will be accrued.

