## Discussion

HEAT is the first clinical trial combining genomics and radiomics to personalize radiotherapy in STS, with the goal of significantly improving treatment response and outcome. This clinical trial utilizes a novel genomic-based algorithm (GARD) and radiomic-habitat directed treatment approach, to safely deliver optimized and escalated isotoxic RT doses (60 or 70 Gy in 25 fractions) to regions of high radioresistance. If successful, this trial would have implications beyond soft tissue sarcoma. We would be demonstrating for the first time that it is possible to improve the clinical outcome of RT-treated patients by integrating biological and radiologic features into clinical trial design and dose determination.

Current studies exploring neoadjuvant treatment intensification for high grade STS are investigating combinational therapies in conjunction with RT. Two such interventional studies that are currently enrolling are the phase 1 “Gemcitabine and Docetaxel With Radiation in Adults With Soft Tissue Sarcoma of the Extremities” study (NCT04037527) and phase 2 “Preoperative IMRT With Concurrent Anlotinib for Localised Extremity or Trunk Sarcoma” study (NCT05167994). An observational study out of Mayo Clinic, “An Imaging Agent (Fluorodopa F 18) With Positron Emission Tomography/​Magnetic Resonance Imaging for Assessing Treatment Response in Patients With High-Grade Soft Tissue Sarcomas” (NCT05560009), is evaluating novel imaging techniques to evaluate RT treatment response. The HEAT trial differs from other contemporary trials because it incorporates genomic and radiomic understanding of STS to craft an individualized and GARD-based treatment to optimize RT dose to radioresistant intratumoral habitats while maintaining clinically acceptable doses to nearby normal structures for high-grade STS.

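### Table 1 does not exclude systemic anticancer therapy before resection, although the 7.9% benchmark is for standard neoadjuvant radiotherapy and the endpoint cannot separate causes of response

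*Protocol article*

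**What the plan says.** Under Inclusion and exclusion criteria the Protocol article states that "All inclusion and exclusion criteria are shown in Table 1". The table lists 14 inclusions and 7 exclusions. Two exclusions concern earlier treatment of the tumour: gross total excision (exclusion 3) and "Prior RT to the region of the study cancer that would result in overlap of RT fields" (exclusion 6). No item mentions chemotherapy or any other systemic anticancer therapy, whether before enrolment or planned before resection. Exclusion 7 covers medical or social reasons for not completing the trial, which a patient on systemic therapy need not have.

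The reference rate is set under Sample size and interim analyses: "The null hypothesis that the true FPR is 7.9"%. The Aims section describes the target as an increase "over historic standard neoadjuvant radiotherapy (7.9%) to 24"%, and the Background says that "standard neoadjuvant radiation treatment achieves a favorable pathological response (FPR ≥ 95% cellular response) in only 8% of cases". A second, institutional rate in GARD modeling of STS is 37 of 202 (18.3%) "STS patients treated with standard neoadjuvant RT alone experienced an FPR".

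The section on radiological and pathological evaluation defines response as necrosis, treatment response and fibrosis together, and places resection three to twelve weeks after radiotherapy. The study has one arm (Study design).

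**The concern.** A single-arm trial attributes to its intervention everything that separates the observed rate from the benchmark. That is fair only if the enrolled patients otherwise resemble those behind the benchmark. Here the benchmark is described as a radiotherapy rate, while the eligibility list, presented as complete, does not limit entry to patients whose only treatment before surgery is radiotherapy. The pathologist's reading cannot tell necrosis or fibrosis due to systemic therapy from that due to radiation.

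If systemic therapy before surgery adds responses, the error runs one way, towards declaring the habitat-directed escalation a success. The boundaries are small counts (5 of 13, 5 of 23, 7 of 36), so a few such responders could decide the result.

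**Working it through.** **Inputs from the Protocol article.** Null 7.9%, alternative 24%, one-sided 5%, stated power 81.8%. Stages of 13, 10 and 13 evaluable patients (Study design). Success at 5 or more of 13, 5 or more of 23, or 7 or more of 36; futility at 2 or fewer of 23 (Sample size and interim analyses). That last section gives ten patients for the third stage. I used 13, because only 13 adds up to 36.

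**Inputs assumed, because the article does not give them.** The share *f* of patients with systemic therapy before resection, and their FPR rate *q* when escalation has no effect.

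**Rule.** Five responders among the first 13 imply at least five among 23, so the stage 1 success adds nothing further. With X the count among 23 and Y the count among the last 13:

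P(success) = P(X ≥ 5) + P(X = 3)·P(Y ≥ 4) + P(X = 4)·P(Y ≥ 3)

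**Reproducing the plan's figure (24%).** 0.6783 + 0.1012 × 0.3822 + 0.1598 × 0.6364 = 0.819, against the stated 81.8%.

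**False success at the null (7.9%).** 0.0311 + 0.1684 × 0.0156 + 0.0722 × 0.0775 = 0.039. This probability reaches 5% at a true rate of 8.4%, half a percentage point above the null.

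**Mixed population, no effect of escalation.** p = (1 − f) × 0.079 + f × q, then the same formula.

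- Mildest case, f = 10%, q = 15%: p = 0.9 × 0.079 + 0.1 × 0.15 = 0.0861. P(success) = 0.0429 + 0.1867 × 0.0208 + 0.0880 × 0.0950 = 0.055.
- Strongest case, f = 20%, q = 30%: p = 0.8 × 0.079 + 0.2 × 0.30 = 0.1232. P(success) = 0.1449 + 0.2388 × 0.0660 + 0.1678 × 0.2096 = 0.196.

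| Share with systemic therapy (assumed) | FPR 7.9% (no added response) | FPR 15% | FPR 20% | FPR 25% | FPR 30% |
|---|---|---|---|---|---|
| 10% | 3.9% | 5.5% | 6.8% | 8.4% | 10.0% |
| 20% | 3.9% | 7.5% | 10.8% | 14.9% | 19.6% |

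**Check of a possible remedy.** Suppose the true rate is 24%, and 10% of patients receive systemic therapy and are counted as non-responders. The rate becomes 0.9 × 0.24 = 0.216, and power falls from 81.9% to about 72%.

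**The case against.** The strongest reply is that silence is not permission. No section says that systemic therapy is given, allowed or expected; the schema and the treatment sections describe radiotherapy followed by resection. The Discussion says of other trials that "Current studies exploring neoadjuvant treatment intensification for high grade STS are investigating combinational therapies in conjunction with RT", and then sets HEAT apart from them, which suggests that radiotherapy alone is intended. The article also condenses a fuller protocol (version 1.4), and a rule on treatment during radiotherapy, or between it and surgery, may stand there.

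Much of this holds. A reader might infer that patients on chemotherapy are being enrolled, or that the primary question cannot be answered. The documents support neither: such patients could enter only because nothing excludes them, and the bias could be nil. Nor does the Discussion sentence show that combinations are common among HEAT patients, since it describes other studies. The words for radiotherapy alone attach to the 18.3% rate, which is not the null. That the 7.9% is free of systemic therapy is a reading of its label; the article does not describe treatment in the trial behind it. The absence of a rule on concomitant treatment, or of an analysis plan for such patients, is not a finding here.

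What survives is narrow. The article declares its eligibility list complete, and that list covers earlier radiotherapy and surgery but not systemic therapy given before enrolment or planned before resection. Condensation does not explain an omission from a list said to be whole.

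**Conclusion.** The point holds as a mismatch between the stated eligibility and the benchmark. Followed as written, Table 1 admits patients whose response could owe something to systemic therapy, and neither the endpoint nor the design can separate that from the effect of dose.

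Its size cannot be computed from the documents. Under the assumed 10 to 20% of patients and FPR of 15 to 30%, with no effect of escalation, the chance of declaring success is about 5.5 to 20% instead of 3.9%. It stays at 3.9% if no patient has such therapy or if it adds no response. The illustration also takes 7.9% as the correct rate for patients with radiotherapy only. It shows how little room the boundaries leave; it does not show that the trial's error rate is inflated. The point is worth correcting because the remedy is cheap, and confidence in its practical weight is moderate.

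**What to change.** Add one exclusion to Table 1: systemic anticancer therapy for the index tumour given before enrolment, or planned before resection. The enrolled population then matches the radiotherapy benchmark. If the full protocol already has such a rule, carry it into the table. This is a matter of who is eligible, not of how any patient should be treated.

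If an enrolled patient nevertheless receives such therapy before surgery, keep one primary denominator for the stage boundaries and report the FPR with and without those patients as a sensitivity analysis. Do not both remove them from the boundaries and count them as non-responders: the two rules contradict each other, and the second costs power, as shown above.

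The cost is one eligibility line and one sentence of analysis. Accrual may be somewhat slower if some candidates are selected for systemic therapy first. No procedures are added.
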